## Abstract

**Background:**

Approximately 15 million persons in the European Union and 10 million persons in the USA are alcohol-dependent. The global burden of disease and injury attributable to alcohol is considerable: worldwide, approximately one in 25 deaths in 2004 was caused by alcohol. At the same time, alcohol use disorders remain seriously undertreated.

In this context, alternative or adjunctive therapies such as brain stimulation may play a prominent role. The early results of studies using transcranial direct current stimulation found that stimulations delivered to the dorsolateral prefrontal cortex result in a significant reduction of craving and an improvement of the decision-making processes in various additive disorders. We, therefore, hypothesize that transcranial direct current stimulation can lead to a decrease in alcohol consumption in patients suffering from alcohol use disorders.

**Methods/design:**

We report the protocol of a randomized, double-blind, placebo-controlled, parallel-group trial, to evaluate the efficacy of transcranial direct current stimulation on alcohol reduction in patients with an alcohol use disorder. The study will be conducted in 14 centers in France and Monaco. Altogether, 340 subjects over 18 years of age and diagnosed with an alcohol use disorder will be randomized to receive five consecutive twice-daily sessions of either active or placebo transcranial direct current stimulation. One session consists in delivering a current flow continuously (anode F4; cathode F3) twice for 13 minutes, with treatments separated by a rest interval of 20 min. Efficacy will be evaluated using the change from baseline (alcohol consumption during the 4 weeks before randomization) to 24 weeks in the total alcohol consumption and number of heavy drinking days. Secondary outcome measures will include alcohol craving, clinical and biological improvements, and the effects on mood and quality of life, as well as cognitive and safety assessments, and, for smokers, an assessment of the effects of transcranial direct current stimulation on tobacco consumption.

**Discussion:**

Several studies have reported a beneficial effect of transcranial direct current stimulation on substance use disorders by reducing craving, impulsivity, and risk-taking behavior, and suggest that transcranial direct current stimulation may be a promising treatment in addiction. However, to date, no studies have included sufficiently large samples and sufficient follow-up to confirm the hypothesis. Results from this large randomized controlled trial will give a better overview of the therapeutic potential of transcranial direct current stimulation in alcohol use disorders.

**Trial registration:**

Clinical Trials Gov, NCT02505126 (registration date: July 15 2015).

## Background

Alcohol use disorder (AUD) is considered a major public health problem in Western societies [1]. Approximately 15 million persons in the European Union and 10 million persons in the USA are alcohol-dependent. The global burden of disease and injury attributable to alcohol is considerable: worldwide, approximately one in 25 deaths in 2004 was caused by alcohol. In the EU in 2004, alcohol was responsible for one in seven male deaths and one in 13 female deaths in the group aged 15–64 years [2]. As alcohol can cause more than 60 diseases (cancer; vascular, endocrine, neurological diseases; etc.), and especially many nonfatal injuries early in life, the disability-adjusted life years (DALYs) are proportionally even higher: 4.6 % of all DALYs were caused by alcohol (men: 7.6 %; women: 1.4 %) [3].

At the same time, AUD remain seriously undertreated. A large treatment gap exists, given than less than 8 % of people in Europe and less than 10.5 % of people in the USA with a diagnosis of any alcohol disorder are actually receiving any treatment [4–7]. One of the main reasons is that these patients are not ready to stop drinking, and thus are not attracted to the abstinence goals proposed by the current psychosocial and pharmacological treatments [8]. The availability of new treatment strategies for reducing alcohol consumption would make it much easier for patients to request help to reduce their alcohol use. Thus, new treatments supporting this strategy are required to improve the care of patients suffering from AUD.

In this context, alternative or adjunctive therapies such as transcranial direct current stimulation (tDCS) and repetitive transcranial magnetic stimulation (rTMS), two noninvasive brain stimulation techniques, may play a prominent role because of their ability to modulate focally the neuronal excitability of superficial brain regions and even deeper structures due to brain connectivity [9]. Indeed, neuroimaging studies in addictive disorders have identified changes in prefrontal regions, in particular in the dorsolateral prefrontal cortex (DLPFC) [10]. These brain changes were associated with craving, manifested by an intense desire or urge for the drug, and with an impaired inhibitory control [9, 11, 12]. Overall, the early results of studies using rTMS and tDCS applied to the DLPFC found a significant reduction in craving in various addictive disorders (tobacco, alcohol, marijuana, and methamphetamine) [12–36]. A meta-analysis of the effects of tDCS and rTMS on the DLPFC, which included 17 of these studies, provided evidence that stimulation can decrease craving levels in various substance-related and addictive disorders [10]. In this meta-analysis, random-effects analysis revealed a pooled standardized effect size (Hedge’s g) of 0.476, indicating a medium effect size, thereby favoring active stimulation over sham stimulation in the reduction of craving. No significant differences were found between the two brain-stimulation techniques, even though their mechanisms of action are somewhat different [10, 37].

Even though these results are encouraging, the large majority of these studies were preliminary, with small sample sizes and without follow-up of the patients. In addition, considerable heterogeneity existed in terms of the sample population, study design, and outcome measurements. In addition, a majority of these studies focused on clinical symptoms such as craving, instead of assessing more global and pertinent therapeutic results such as reduced consumption or maintenance of abstinence, which are the ultimate therapeutic goals for patients with substance-related and addictive disorders.

Thus, in a randomized controlled trial (RCT) involving a large sample, we propose to evaluate, for the first time, the clinical benefits of tDCS on the reduction of consumption in patients with AUD.

### Aims

The principal objective of this study is to evaluate, in nonabstinent patients with AUD, the efficacy of 1 week of tDCS (five consecutive twice-daily sessions) versus placebo in reducing alcohol consumption within the 24 weeks following the treatment. The hypothesis is that tDCS, by inducing changes in the neuronal activity of the DLFPC to decrease the craving, can lead to a decrease in the consumptions of alcohol in patients suffering from AUD.

In addition, we will assess the effects of tDCS on mood, cognitive behavior, and quality of life and, in participants who have AUD combined with tobacco use disorder (TUD), the effect of tDCS on tobacco craving and consumption.

## Methods/design

### Overview

This is a multicenter, randomized, placebo-controlled, double-blind, parallel-group study comparing five consecutive two-daily sessions of active tDCS versus placebo tDCS (Fig. 1). The study is carried out in the psychiatric or addictology departments of 14 centers in France and Monaco and aims to recruit 340 patients with AUD over the course of 2 years.

**Fig. 1 Fig1:**
[figure not shown]
Study flow diagram

The study protocol was approved by the independent ethics committee (Committee for the Protection of Persons, EST III) on 22 June 2015 under number 2015-A00576-43 and by the French National Agency for the Safety of Medical Products and Devices (Agence National de Sécurité des Médicaments et des Produits de Santé). After participants have been provided with a complete description of the study, written informed consent will be obtained from each participant.

### Inclusion criteria

Patients eligible to be enrolled in this trial according to the following criteria will be invited to take part: (1) male and female patients over 18 years of age, (2) who meet the criteria for mild to severe AUD defined in the Diagnostic and Statistical Manual of Mental Disorders-Fifth edition (DSM-5) [11], (3) are motivated to reduce their alcohol consumption, and (4) have experienced at least one prior attempt to achieve abstinence (unsuccessful or relapse) or to reduce alcohol consumption. This last criterion was included to ensure that participants had attempted the usual methods to treat AUD before consenting to participate in a study that assesses an experimental treatment.

### Exclusion criteria

Patients will be excluded if they are identified, at the inclusion visit, as having any of the following: (1) a breath-alcohol concentration (BAC) > 0 milligrams per liter of exhaled air; (2) fewer than six heavy drinking days (HDD) in the previous 4 weeks (a day with alcohol consumption ≥ 60 g for men and ≥ 40 g for women) [1]; (3) an average alcohol consumption below the medium risk level according to World health Organization (WHO) in the previous 4 weeks (≤40 g/day for men; ≤ 20 g/day for women) [38]; (4) > 3 days of abstinence prior to inclusion; (5) a revised Clinical Institute Withdrawal Assessment for Alcohol (CIWA) score ≥ 10 (indicating the need for medication-supported detoxification); (6) recent (within 1 month prior to the inclusion) treatment with disulfiram, acamprosate, topiramate, baclofene, naltrexone, and nalmefene; (7) a history of pre-delirium tremens and delirium tremens; (8) DSM-5 substance-use disorder other than an alcohol or nicotine use disorder; (9) acute psychiatric disorders that have required hospitalization and/or immediate adjustment of psychotropic medications; (10) major depression, as defined by the Hamilton Depression rating scale (HAM-D) greater ≥ 24 [39]; (11) recent change in psychotropic medication (<1 month); (12) severe chronic psychiatric disorders including schizophrenia, paranoia, or bipolar disorder type I and II; (13) advanced liver, kidney, cardiac, or pulmonary disease or other acute serious or unstable medical conditions that would compromise a patient’s participation in the study according to the physician’s judgment; (14) contraindications to tDCS, e.g., metal in the head or medical devices implanted in the brain; (15) women who are pregnant or lactating; (16) women of childbearing potential with a positive urine β–human chorionic gonadotrophin pregnancy test at inclusion; (17) concurrent participation in another trial, employees of the investigator or trial site, or patients protected by law; (18) persons who are not covered by national health insurance; (19) patients, who, in the opinion of the investigation, are not able to complete the alcohol timeline follow-back (TLFB) and to complete their daily alcohol consumption in a diary (derived from the TLFB) during the 3 months of the study; and (20) patients who refused to sign the “safety agreement”.

The “safety agreement” is a paper contract that expressly notes that if a participant comes to the hospital for a visit or a tDCS session using his/her own car and has a BAC > 0.25 milligrams per liter of exhaled air (which prohibits a person from driving a car in France), he/she will agree to give his/her car keys to the medical staff and authorize the staff to call a member of his/her family or a friend to take the patient home if the patient is unable to use public transport.

### Study process

The study will have three phases (Fig. 1):During the first phase, subjects will be screened using the inclusion and exclusion criteria. Information on the implementation of the study and the objectives of the research will be given to each subject. Inclusion and tDCS treatment will be scheduled in the following weeks for eligible participants.The second phase will correspond to both the inclusion of participants and the period of the tDCS sessions. This phase will always begin on Monday with five steps: (1) participants will be evaluated for study eligibility based on the inclusion and exclusion criteria; (2) they will have to sign the informed consent and the “safety agreement” after it has been ascertained that the participant has a zero alcohol-blood level using breath alcohol concentration; (3) a clinical (including alcohol TLFB) and biological baseline assessment will be performed (visit 1); (4), included participants will be randomized to active or placebo tDCS; and (5), the first tDCS will be delivered.Then, daily sessions will be performed during the following days up to Friday. The second phase will end by a clinical assessment (visit 2) once the last tDCS session has been delivered.The third phase will be a 6-month follow-up phase without treatment. A clinical assessment will be performed every 4 weeks (visits 3 to 8), and the biochemical markers of alcohol consumption will be measured at 1, 3, and 6 months after the end of the stimulation (visits 3, 5, and 8).

### Interventions

For tDCS, a StarStim wireless tDCS neurostimulator (Neuroelectrics, Barcelona, Spain) will be used. It can deliver a maximum current of plus/minus 2 mA per electrode. Direct currents will be applied via a pair of 0.9 % NaCl-soaked surface sponge electrodes (25 cm^2^). According to the 10–20 international system, the anode will be placed over F4 (right DLPFC), and the cathode, over F3 (left DLPFC). Patients will receive two consecutive 13-min anodal tDCS sessions (2 mA) per day on 5 consecutive days. The two daily tDCS sessions will be separated by an interval of 20 min. Each of the two sessions will have a ramp-in and ramp-out of 15 s each. This pattern of stimulation (anode F4; 13:20:13 min) is in accordance with the study of Klauss, who found that these stimulation parameters for tDCS had a long-lasting, beneficial, modulatory effect on alcohol-use relapse at 6 months [12].

The StarStim wireless tDCS neurostimulator includes a study mode for double-blind studies. The study mode encodes sham and active stimulation. Numerous sham and active stimulation protocols will be created and numbered without providing information related to the set-up. At the inclusion of a patient, the administrator will assign the subject to one of the protocols previously recorded in StarStim. During the stimulation, the operator will not have access to protocol data to preserve double-blinding. Sham stimulation will be given using a similar pattern of stimulation to that in the active group. With sham stimulation, the initial ramp-up phase of 15 s (also up to 2 mA) will be immediately followed by a ramp down phase of 30 seconds. A second ramp-up (30 s) and down (15 s) phase will be delivered 13 min later in order to envelop the beginning and the end of a session’s stimulation. Using this pattern of sham stimulation, we hope to improve sham conditions both for participants and assessor blinding by inducing skin sensation and skin redness in the immediate poststimulation period, even though no 13-minute stimulation period occurred.

### Randomization

Randomization will be performed directly though the secure CleanWebTM internet-based software after identification of the investigator by a personal password (website https://chu-dijon.tentelemed.com). The inclusion criteria and the absence of exclusion criteria will be validated before the randomization can be done. Investigators and patients will be blinded to the treatment assignment. The treatment algorithms will be determined by the study statistician. This allocation will be based on a minimization technique taking into account the center. Patients will be randomly assigned to one of the two groups in a 1:1 ratio. A comprehensive document describing the randomization procedure will be kept in a confidential manner at the Unité de Soutien Méthodologique, Direction of Clinical Research, University Hospital of Dijon, Francel.

### Outcomes

In the “*Guideline on the development of medicinal products for the treatment of alcohol dependence,*” for an alcohol reduction strategy, the European Medicines Agency (EMA) recommend using a co-primary efficacy outcome, the change from baseline in total alcohol consumption (TAC) per month and a reduction in the number of heavy drinking days (HDD) [1]. Thus, our principal effective criteria on alcohol reduction will be both the change in TAC from baseline to week 24, defined as mean daily alcohol consumption over 28 days (in g/day), and the number of HDD, defined as more than 60 grams of pure alcohol in men and 40 grams in women consumed in one day. Baseline will be defined as alcohol consumption during the 28 days before randomization using the alcohol TLFB method, a validated method that retrospectively obtains estimates of daily drinking using a calendar [40, 41].

The secondary evaluation criteria will be the change from baseline to the end of the tDCS cessions and, then, for each 4-week period after the treatment up to week 24 in the following parameters:TAC (g/day) and number of HDDProportion of subjects with a significant categorical shift in World Health Organization (WHO) risk levels of drinking: low risk (*H* ≤ 40 g/d; *F* ≤ 20 g/d), medium risk (*H* ≤ 60 g/d; *F* ≤ 40 g/d), high risk (*H* ≤ 100 g/d; *F* ≤ 60 g/d, and very high risk (*H* > 100 g/d; *F* > 60 g/d) [38]Proportion of subjects with a 50 %, 70 %, and 90 % reduction in alcohol consumption, as well as, the proportion of patients who potentially achieve abstinenceLevel of alcohol dependence severity (alcohol dependence scale)Craving/urge to drink assessment (visual analog scale, obsessive compulsive drinking scale)Clinical global impression—severity and improvementScores for depression scales (Hamilton depression rating scale—17 items)Quality of life (short form health survey—12 items)

Other secondary evaluation criteria will include the change from baseline at week 4, week 12, and week 24 after the treatment, in the following:Biochemical alcohol consumption markers (gamma glutamyl transferase, mean corpuscular volume, aspartate aminotransferase, alanine aminotransferase, and carbohydrate deficient transferrin)Cognitive assessment (Montreal cognitive assessment)Number of cigarettes smoked/day and craving for tobacco (visual analog scale, tobacco-craving questionnaire) for smokers.

The number of patients with adverse events will be determined at the time of each visit.

### Sample size calculation

As the primary efficacy outcome, the EMA recommends using both TAC and the number of HDD [1]. Besides, any reduction in total alcohol consumption of at least 10 g/day for patients with alcohol use disorders will reduce the annual and lifetime risk of alcohol-related death [3].

In this context, a sample size calculation based on an expected difference between the treatment groups of 10 g/day in total alcohol consumption, with a standard deviation for the TAC of 30 g/day and with an autocorrelation of 0.7 between observations in the same subject, indicates that 274 patients would be required.

By considering a significance level of 1.25 % (co-primary outcome), a power of 80 %, and with the hypothesis of a premature drop-out or a noninitiation of the treatment (acute repeated alcoholism) for 20 % of the patients, 340 patients (170 per group) should be included to meet the objectives of the study.

### Statistical analysis

All randomized patients will be used for the efficacy analyses. The baseline and demographic characteristics of the two groups (active tDCS vs placebo tDCS) will be recorded. Qualitative variables will be described in terms of numbers and percentages, and quantitative variables, in terms of means and standard deviations or medians and interquartile intervals. The co-primary outcome of change in TAC from baseline and reduction in the number of HDD at 6 months after treatment and its association with tDCS will be analyzed under the intention-to-treat principle using mixed model repeated measures (eight times).

The comparability of the two groups at baseline will be evaluated using the chi square test or Fisher’s test for qualitative variables, and Student’s T test or the Mann Whitney test for continuous variables. Then, a mixed model repeated measures will be conducted to estimate the effect of treatment on the TAC first, and HDD second. Observed cases will be considered random effects, and the site, sex, time, and treatment as the fixed effects. We will use multiple imputation techniques to compensate for any potential bias introduced by missing endpoint data [42].

For the primary outcome, per-protocol analysis will also be conducted among the participants who have completed baseline and endpoint assessments. The secondary outcome measurements will be analyzed with similar models to those used for the co-primary, continuous variables, and logistic regression, for dichotomized outcomes.

All tests will be one-sided. The primary results will be examined at a significance level of 0.0125 (co-primary outcome). For secondary outcomes, the threshold for significance will be fixed at 0.025. All analyses will be performed using SAS version 9.3 (SAS Institute, Inc, Cary, NC, USA) by the team of statisticians of the Unité de Soutien Méthodologique, Direction of Clinical Research, University Hospital of Dijon, France.

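### The primary endpoint is the week-24 change, but the primary model as listed has only main effects over eight times and gives a treatment difference pooled over visits

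*Protocol article*

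**What the plan says.** Under Outcomes, the primary criterion for total alcohol consumption (TAC) is "the change in TAC from baseline to week 24, defined as mean daily alcohol consumption over 28 days (in g/day"; the number of heavy drinking days (HDD) is its co-primary. Statistical analysis repeats the time point: "reduction in the number of HDD at 6 months after treatment". TAC and HDD in each successive 4-week period up to week 24 are listed separately, as secondary criteria.

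The primary outcome "will be analyzed under the intention-to-treat principle using mixed model repeated measures (eight times"). The terms are then given: "Observed cases will be considered random effects, and the site, sex, time, and treatment as the fixed effects".

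Study process lists eight visits. At the first, before randomization, a clinical and "biological baseline assessment will be performed (visit 1"). Of the next it says: "The second phase will end by a clinical assessment (visit 2) once the last tDCS session has been delivered". Visits 3 to 8 follow at 4-week intervals. The article does not say which eight times enter the model, or what look-back period visit 2 uses for drinking.

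**The concern.** A model with treatment and time as main effects only assumes the same treatment difference at every time. Its treatment coefficient is a weighted average over all modelled times, and nothing in it isolates week 24.

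Two errors can follow. An early effect that has gone by week 24 can be declared a success on an endpoint defined at week 24. A sustained effect can be diluted by times that carry little or none of it: baseline if it is among the responses, and possibly visit 2, four days after the first stimulation. Stimulation lasts one week, and the Discussion names durability as a particular question, so the distinction between an average and week 24 is central here.

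**Working it through.** **Inputs.** From Sample size calculation: difference 10 g/day, SD 30 g/day, within-subject correlation 0.7, 340 patients with 20% loss (340 × 0.8 = 272, or 136 per arm). From Statistical analysis: one-sided 0.0125, so z = 2.2414.

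**The plan's own figure.** For the mean of m equally correlated measures the variance factor is (1 + (m − 1) × 0.7)/m. With m = 3 this is 0.80, and 2 × 900 × 0.80 × (2.2414 + 0.8416)²/10² = 136.9, so 137 per arm, or 274 as stated. The article does not state m = 3. The mean of eight measures would need 254, and a single week-24 change 206. Another combination also gives 274 (two-sided 0.0125, AR(1), four measures), so the figure does not settle which quantity was meant.

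**Counting times.** Visits 2 to 8 are seven. Eight is reached only by adding visit 1.

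**Assumptions for the illustration.** Complete data, normal approximation, and visit 2 carrying 4/28 of the week-4 effect. AR(1) treats the eight visits as equally spaced. The effect patterns are mine, not the plan's. The chance of success is Φ(estimate/SE − 2.2414).

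**Eight-time model on raw TAC.**
- Compound symmetry: every visit has weight 1/8. Variance 900 × (1 + 7 × 0.7)/8 = 663.75; SE = √(2 × 663.75/136) = 3.124.
- AR(1): the first and last visits have weight 1/3.8 = 0.263, the others 0.3/3.8 = 0.079. Variance 900 × 1.7/3.8 = 402.6; SE = 2.433.

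*Fading effect* (visits 3 to 8: 10, 8, 6, 4, 2, 0; visit 2: 1.43; baseline 0):
- Compound symmetry: 31.43/8 = 3.93; Φ(3.93/3.124 − 2.2414) = 16%.
- AR(1): 0.079 × 31.43 = 2.48; Φ(2.48/2.433 − 2.2414) = 11%.

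*Sustained effect* (10 at visits 3 to 8; visit 2: 1.43; baseline 0):
- Compound symmetry: 61.43/8 = 7.68; Φ(7.68/3.124 − 2.2414) = 59%.
- AR(1): 0.079 × 51.43 + 0.263 × 10 = 6.69; Φ(6.69/2.433 − 2.2414) = 69%.

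**Change from baseline, baseline not a response.**
- Visits 3 to 8, compound symmetry: variance 900 × (0.75 + 1 − 1.4) = 315; SE = 2.152. Fading: 30/6 = 5.00, success 53%. Sustained: 10, power 99%.
- Visits 2 to 8, compound symmetry: variance 900 × (0.743 + 1 − 1.4) = 308.6; SE = 2.130. Fading: 31.43/7 = 4.49, success 45%. Sustained: 61.43/7 = 8.78, power 97%.
- Visits 2 to 8, AR(1), generalized least squares: fading estimate 1.89, SE 2.707, success 6%. Visit 2 has weight of about 0.79 here.

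The fading pattern thus gives about 6% to 53%. Another share of the effect at visit 2 would move every figure that includes that visit, most of all the last.

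**Week-24 contrast, 136 per arm, effect 10 g/day at week 24.** SE = √(2 × 900 × f/136).

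| Baseline to week-24 correlation | Analysis | f | SE | Power |
|---|---|---|---|---|
| 0.7 | change score | 2(1 − 0.7) = 0.60 | 2.818 | 90% |
| 0.7 | baseline-adjusted | 1 − 0.7² = 0.51 | 2.598 | 95% |
| 0.7⁷ = 0.082 (AR(1)) | change score | 1.835 | 4.929 | 42% |
| 0.7⁷ = 0.082 (AR(1)) | baseline-adjusted | 0.993 | 3.626 | 70% |

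**The case against.** The article condenses a fuller plan, and interactions and contrasts are often left to that plan. This partly stands: one can say that no treatment-by-time term is stated, not that none will be fitted. But the article does give a list of terms, and that list does not deliver the endpoint it names.

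The Aims section describes the objective as lower consumption over the 24 weeks after treatment, which suits a follow-up average, and the sample size fits an average of three measures. This also stands as a real ambiguity. Yet Outcomes and Statistical analysis both fix the primary criterion at week 24 or 6 months, and no follow-up average should include a pre-randomization value.

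Baseline as a response is inferred from the visit count. If change is the response, the baseline record is zero for everyone and would presumably be left out. With a treatment-by-time term, raw baseline among the responses would be legitimate. The pooling problem does not depend on this: with visits 3 to 8 alone, the fading effect still succeeds in up to 53% of trials. Nor do the documents say that visit 2 uses a 28-day window overlapping baseline.

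A reader might also take the phrase about observed cases to mean that observations are treated as independent. With a design effect of 1 + 7 × 0.7 = 5.9, the true SE would be 2.43 times the nominal one and the type I error about 18%. The documents do not support that reading: the model is a repeated-measures mixed model, and the sample size assumes correlation of 0.7 within a subject. The phrase is most sensibly loose wording for patients.

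**Conclusion.** The point holds for the model as stated: its treatment coefficient is a pooled difference, not the week-24 effect, and it can succeed on an effect that has vanished by week 24. The size is uncertain. For the assumed fade from 10 g/day to zero, the chance of success runs from about 6% to 53%, against a nominal 1.25%. Dilution of a sustained effect is material if raw TAC is modelled over eight times (about 6.7 to 7.7 g/day instead of 10; power about 59% to 69%) but negligible for a change score under compound symmetry (97% against 99%). A general loss of power therefore cannot be claimed. The same structural point applies to HDD, for which the article gives no variance and no figure can be computed.

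**What to change.** Before unblinding, restate the primary analysis. Take the post-treatment windows at visits 3 to 8 as responses. Fit treatment, time, treatment-by-time, site, sex and the baseline value, with the patient as the unit of within-subject correlation, and make the treatment contrast at week 24 the primary test, for TAC and then HDD. Keep the follow-up average as a secondary result. State which times replace the present eight, report visit-2 drinking over its own stated period, and write patients in place of observed cases as a clarification of wording. Reconcile the Aims with Outcomes and Statistical analysis, so that one time frame is primary.

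This needs no new data. The cost is precision: a week-24 contrast can be less precise than an average. Under compound symmetry at 0.7 its power is still about 90% to 95% with 136 per arm. If correlation decays as AR(1) it falls to about 70% baseline-adjusted and 42% as a change score, which favours adjusting for baseline.

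### The analysis labelled per-protocol is defined by attending the endpoint assessment, not by receiving stimulation, so it is a completers analysis

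*Protocol article*

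**What the plan says.** The Statistical analysis section of the Protocol article puts all randomized patients into the efficacy analyses and analyses the co-primary outcomes by intention to treat, with a mixed model for repeated measures. It then adds a supportive analysis of the primary outcome: a "per-protocol analysis will also be conducted among the participants who have completed baseline and endpoint assessments". That is the whole definition given.

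Three other places bear on it:

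- Sample size calculation allows for 20% of patients being lost, "with the hypothesis of a premature drop-out or a noninitiation of the treatment (acute repeated alcoholism"). Non-initiation is thus an expected event.
- Study process places randomization before the first stimulation on the same day. One treatment week is followed by six months without treatment, with a visit every 4 weeks.
- Interventions plans two 13-minute stimulations a day for 5 days, so 2 × 5 = 10 per patient.

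**The concern.** A per-protocol analysis is read as the effect among patients who were treated as planned. Here the entry rule says nothing about treatment. Stimulation is confined to the first week and the endpoint lies about six months later, so having an endpoint assessment tells little about how many of the ten stimulations a patient received.

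Two things are at stake. First, untreated patients in the active arm dilute the estimate that is meant to describe treated patients. Second, the set selects on staying in the study, which happens after randomization and may depend on drinking, the outcome itself. If this analysis and the intention-to-treat analysis agree or disagree, the reader cannot say whether that reflects treatment received or who stayed.

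**Working it through.** **Step 1. Apply the stated rule to four kinds of randomized patient.**

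| Stimulation received | Endpoint assessment | In the set as written | In a set defined by treatment received |
|---|---|---|---|
| All ten | Yes | Yes | Yes |
| All ten | No, but earlier visits attended | No | Yes |
| None | Yes | Yes | No |
| None | No | No | No |

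The rule and the label disagree in the second and third rows. Both kinds of patient can occur, because randomization precedes the first stimulation, non-initiation is expected, and follow-up runs for six months after treatment ends.

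**Step 2. Reproduce the plan's sample size, to have a base for the illustration.** Inputs from Sample size calculation: a group difference of 10 g/day, an SD of 30 g/day, a level of 0.0125 and 80% power; the correlation and the resulting total are given as "with an autocorrelation of 0.7 between observations in the same subject, indicates that 274 patients would be required". Sidedness comes from Statistical analysis: "All tests will be one-sided".

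- Variance factor for the mean of m measures with correlation 0.7: f = (1 + (m − 1) × 0.7)/m. With m = 3, f = 2.4/3 = 0.80.
- n per arm = 2 × (2.241 + 0.842)² × 30² × 0.80/10² = 2 × 9.505 × 7.2 = 136.9, so 137 per arm and 274 in total. This matches.
- Allowance for loss: 274/0.80 = 342.5, against the planned 340.

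The article does not state m. The value 3 is inferred because it returns 274 exactly. The present point does not depend on it.

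**Step 3. Dilution by untreated members.** Let q be the share of active-arm members of the set who had no stimulation. Assume that they gain nothing and are otherwise comparable. The expected difference is then 10 × (1 − q). Power is Φ(difference/SE − 2.241), with SE = 30 × √0.80 × √(2/137) = 3.242 g/day and 137 per arm.

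| q (assumed) | Difference, g/day | Power |
|---|---|---|
| 0% | 10.0 | 80% |
| 10% | 9.0 | 70% |
| 20% | 8.0 | 59% |

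The documents give no value for q. The 20% row borrows the whole loss allowance and is an outer illustration.

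**Step 4. Selection on retention.** An illustrative simulation used SD 30 g/day, correlation 0.7 and a true effect of −10 g/day. The dropout models are assumed.

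- *Dropout rises with drinking already recorded, by the same rule in both arms.* Dropout came to 23.5% and 23.1% in the sham arm, against 18.1% and 15.3% in the active arm, for a weaker and a stronger dependence. Completers gave −8.84 and −7.85. The mixed model on all patients gave −9.97 and −10.16, against full-data values of −9.99 and −10.14.
- *Dropout forced to be equal in the two arms, same dependence.* Completers gave −10.15 and −10.04, against full-data values of −10.09 and −9.97, so essentially no bias.
- *Dropout driven by unobserved drinking in the active arm only, at about 20% in each arm.* Completers gave −14.37 and −16.77, against full-data values of −10.06 and −9.97.

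The completers figure can therefore be unbiased, too small or too large. It compares endpoint means without baseline adjustment, so it shows that the bias can go either way and does not predict its size in this trial.

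**The case against.** The strongest reply is that this is a labelling fault in a secondary analysis. Non-initiators are not lost from the trial's main result, since every randomized patient is analysed by intention to treat. The dilution figures also need non-initiators to attend at week 24, whereas the sample size section counts non-initiation within the 20% loss. If none of them return, q is 0 and there is no dilution. All of this stands. It limits the consequence but does not repair the definition: the rule as written admits untreated patients, excludes treated ones and still selects on retention.

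A reader might go further and infer that relapse-driven dropout is left unaddressed and that imputation is idle. The article says "We will use multiple imputation techniques to compensate for any potential bias introduced by missing endpoint data", and a mixed model is already valid when data are missing at random. The document does not support that inference:

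- It states no imputation model and no missing-data assumption. Auxiliary variables or departures from missing at random may be set out in the SAP or full protocol, which are not shown.
- Relapse that shows in recorded drinking before dropout is handled under missing at random, as Step 4 illustrates.
- The parenthesis on acute repeated alcoholism directly follows non-initiation and may explain only that. It does not establish that later dropout is caused by drinking.

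**Conclusion.** The point holds for the per-protocol set alone. As defined, it is a completers set: it does not estimate the effect in treated patients, and it cannot serve as a check on dropout. This follows from the article's own words and needs no assumption.

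The size does need assumptions. About 9 instead of 10 g/day requires 10% of active-arm members of the set to be unstimulated, to have no benefit and to be otherwise comparable. Over 0% to 20% the range is 10 to 8 g/day. The selection bias may be near zero when dropout is equal in the two arms and its dependence on drinking is the same, and may go in either direction otherwise.

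It would be wrong to conclude that non-treatment undermines the primary result. The intention-to-treat analysis of all randomized patients is untouched. No finding is made on the multiple imputation or on sensitivity analyses.

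**What to change.** Before unblinding:

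1. Define the per-protocol set by treatment received, as a pre-specified minimum number of the planned stimulation sessions applied in the same way in both arms, together with absence of major protocol deviations listed in advance. The study team must choose the minimum.
2. Analyse all available visits of these patients with the same mixed model as the primary analysis, so that a treated patient without an endpoint assessment still contributes.
3. Rename the present set completers, or drop it.

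The cost is a few lines of wording and a little programming. The per-protocol set may become smaller, because untreated attenders leave it, though treated patients who missed the endpoint come in. Sample size, trial conduct and the primary analysis do not change.
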